#### Measurement of intervention intensity control

The ratings of perceived exertion and perceived mental exertion will be measured with the help of teachers immediately after each intervention to help adjust and identify the intensity of PA and the difficulty of the cognitive challenges that are most appropriate for EF interventions for young children. The Borg Category-Ratio 10 scale (Borg CR-10) [71] has been widely used to assess the intensity of perceived PA, which is a judgment of one’s own bodily effort to complete a given behavior. The scale has 10 levels (1–10), with 1 indicating no exertion and 10 indicating maximum exertion. As the participants are young children aged 3–5 years, the scale will be cartooned, and additional descriptions will be provided to ensure that young children are able to select the most relevant option.

### Evaluation of implementation

A comprehensive implementation and process evaluation will be conducted alongside the CRXO trial. Weekly teacher workshops and fidelity checklists will ensure adherence to the intervention protocols. Session logs and teacher attendance records document the amount of intervention delivered. Focus groups with teachers (6 kindergartens randomly selected, 5–6 people in each group) and interviews with principals (6 kindergartens randomly selected) will explore experiences, challenges, and facilitators related to implementation.

### Data analysis

Descriptive statistics (means and standard deviations) will be calculated for all subscales across all measurements. Missing data will be calculated via maximum likelihood estimation via SAS version 9.4 (Cary, NC, USA). Given the characteristics of behavioral intervention research, we will not assume that the collected data will conform to a normal distribution and will be independent of each other. Therefore, a linear mixed effects (LME) model (from the R library NLME, R version 3.4.4) will be used to analyze the associations of different interventions with EF. The number of intervention days (time) was considered to have a possible association with intervention effects [72], so the interaction between the two will be included in the model. Fixed effects will include the intervention days and group, whereas the cluster (i.e., kindergarten) will be treated as a random effect. The LME model will be generated via the R NLME package. A p value less than 0.05 is recognized as a significant difference. Tukey’s honestly significant difference (HSD) test will be used to determine whether there is a significant difference between the interventions [73]. In addition, the false discovery rate-corrected *p* value will be used to determine if there is a statistically significant difference between the interventions. A value less than 0.05 is considered significant. Secondary outcomes (including cognitive difficulty, PA intensity, and teacher attendance) will be similarly assessed via the LME model.

An exploratory factor analysis of the possible static associations between FMS and EF will be conducted, which will be analyzed via partial least squares structural equation modeling (PLS-SEM), since PLS can maximize the prediction capability [74] and can address formative indicators as well as reflective indicators [75]. The relationship between PL and EF will be assessed via Pearson’s correlation coefficient. The effect size (Cohen’s *d*) will be calculated by dividing the difference between the post-intervention means of the two groups by their pooled standard deviation (SD).

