### Sample size calculations

The sample size is calculated using G*Power version 3.1, which is based on the assumed effect size and dropout rates. In a previous systematic review, the effect size of using FMS alone or cognitive challenges alone as an intervention was medium, whereas the effect size of combined FMS and cognitive challenges ranged from small to large [8]; thus, we assumed that the effect size for the current intervention would be medium (f = 0.3), α = 0.05, and power = 0.80, resulting in a total sample size of at least 82 young children [42]. Additionally, we assumed a participant dropout rate of 20%, resulting in a total sample size of at least 103 young children. This study is a four-arm cluster randomized crossover trial that will involve 18 kindergartens from different districts, and it is estimated that there will be 11 children in each class, so the total number will be 18*4*11 = 792, which meets the minimum requirement of the required sample size.

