### Strengths and potential limitations

There are several strengths of this protocol. The four-arm cluster randomized crossover design is particularly suitable for educational research, as it effectively controls for cluster-level confounding variables by allowing each class to serve as its own control. This approach helps manage the influence of cluster-level confounding variables, such as the school environment or teacher characteristics, thereby increasing the statistical efficiency of the analysis [38]. Furthermore, this study addresses the issue of poor methodological quality that has been identified in previous intervention research [8] by employing a comprehensive assessment battery composed of validated and objective measurement tools. The implementation of the program by teachers within their natural kindergarten setting further enhances the ecological validity of the study, making its findings more translatable to everyday educational practice.

There are several foreseeable operational challenges. A principal concern is maintaining intervention fidelity, as it can be challenging to ensure that teachers accurately implement four different intervention programs over a 10-month period. To address this issue, this study included weekly teacher training workshops, a detailed course manual with clear instructions, and the use of questionnaires to monitor compliance. Teachers’ attendance at these workshops will also be recorded and analyzed as a potential factor influencing the effectiveness of the intervention. A 6-week washout period after each intervention also helped reduce teacher fatigue and boredom. Another challenge is the potential for carry-over effects. Although we set a washout period that is twice the intervention period, which is more conservative than previous CRXO studies, there is still no evidence to prove the optimal washout period setting for this type of cognitive or educational research. Finally, as a long-term intervention, there may be a high dropout rate and missing data, as well as a high probability of participant loss at the three follow-up tests after the intervention.

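### The missing-data sentence has scores calculated in SAS but the mixed model fitted in R; if one completed data set is analysed as observed, standard errors and p values are too small

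*Protocol article*

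**What the plan says.** The protocol article, Data analysis, deals with missing data in one sentence: "Missing data will be calculated via maximum likelihood estimation via SAS version 9.4". What is to be calculated there is the missing data themselves. The analysis model comes two sentences later and in another program: "a linear mixed effects (LME) model (from the R library NLME, R version 3.4.4) will be used to analyze the associations of different interventions with" executive function. The section then repeats that "The LME model will be generated via the R NLME package", and says of the random part "whereas the cluster (i.e., kindergarten) will be treated as a random effect".

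Inference is by p value: "A p value less than 0.05 is recognized as a significant difference", followed by Tukey's HSD and a false-discovery-rate correction. The article mentions no confidence intervals.

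On the amount of missing data, Sample size calculations says "we assumed a participant dropout rate of 20%, resulting in a total sample size of at least 103 young children". Strengths and potential limitations warns that "there may be a high dropout rate and missing data" and adds that loss at the three follow-up tests is likely.

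**The concern.** Maximum likelihood for incomplete data normally works inside the model fit. The likelihood is built from the observed scores, and no missing score is ever computed. That would take place in R, where the model is fitted, and SAS would have nothing to do. A SAS step affects an R analysis only if SAS hands something over, and the only product the sentence names is the missing data. Hence the natural reading: predicted scores are filled in, and R analyses the completed file.

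If that file is a single one and is analysed as though every score had been observed, two things go wrong. Predicted values have no residual scatter, so the residual variance is understated. Each filled-in score also counts as a full observation. The estimates hardly change, but their standard errors shrink and the p values shrink with them. Tukey and false-discovery-rate adjustments cannot repair this, because they start from the same standard errors or p values.

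**Working it through.** **Inputs from the article.** 18 × 4 × 11 = 792 children; four conditions, each received in turn; 20% participant dropout. The article gives no figure for the missing-data step itself. The dropout arithmetic reproduces: 82 / (1 − 0.20) = 102.5, rounded up to 103.

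**Assumptions, not in the article.** Within-child correlation 0.3 to 0.7; leavers go at period 2, 3 or 4 with equal probability; missingness unrelated to the scores; total variance 1.

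**From dropout to missing values.** A child leaving at period 2, 3 or 4 loses 3, 2 or 1 of four scores, on average 2 of 4. So 20% of children leaving means 0.20 × 2/4 = 10% of values missing. A second case takes 20% of values missing directly.

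**Rough formula.** Let a share m of n scores be missing and filled with predicted means.
- Valid standard error: σ/√(n(1 − m)).
- Standard error reported from the filled data: σ√(1 − m)/√n, because the variance shrinks by (1 − m) while n is counted in full.
- Ratio: 1 − m. Coverage of a nominal 95% interval: 2Φ(1.96(1 − m)) − 1.
- m = 0.10: ratio 0.90, coverage 0.922. m = 0.20: ratio 0.80, coverage 0.883.

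One random draw per missing score, instead of a predicted mean, gives a ratio of √(1/(1/(1 − m) + m)). At m = 0.20 this is √(1/1.45) = 0.83, coverage 0.896. Adding scatter helps only a little if there is still just one completed data set.

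**Simulation in the crossover layout.** 792 children in 72 classes of 11, four sequences, four periods, no true condition effect, a child random intercept, 400 trials per setting. Maximum likelihood on the observed scores was compared with the same model fitted after filling in maximum-likelihood predicted scores.

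| Missingness | Correlation | SE, observed data | SE, filled data | Ratio | Coverage, observed | Coverage, filled |
|---|---|---|---|---|---|---|
| 20% of children leave (10% of values) | 0.3 | 0.0446 | 0.0395 | 0.886 | 0.950 | 0.927 |
| 20% of children leave (10% of values) | 0.7 | 0.0293 | 0.0256 | 0.875 | 0.945 | 0.915 |
| 20% of values | 0.3 | 0.0479 | 0.0367 | 0.766 | 0.945 | 0.858 |
| 20% of values | 0.7 | 0.0319 | 0.0237 | 0.744 | 0.953 | 0.840 |

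Ratios are from unrounded standard errors. With 400 trials the Monte Carlo error of a coverage near 0.95 is √(0.95 × 0.05/400) = 0.011.

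The true spread of the estimate was the same under both approaches (for example 0.0485 for each at 20% of values missing and correlation 0.3). Filling in therefore added no information; only the reported standard error changed, from 0.0479 to 0.0367.

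The simulated ratios lie below 1 − m because these contrasts are largely within-child. Per child, the within-child degrees of freedom are really 4(1 − m) − 1 but are counted as 3. This suggests a lower guide of (4(1 − m) − 1)/3, which is 2.6/3 = 0.867 at m = 0.10 and 2.2/3 = 0.733 at m = 0.20. The simulated values fall between the two guides.

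**The case against.** The strongest reply is that the article never describes this procedure. It does not use the word imputation, does not mention a completed data set, and does not say that anything passes from SAS to R. The sentence follows the one on descriptive statistics, and may be a loose description of likelihood-based handling, which is valid under missing at random. How the two programs connect could be left to a fuller document. This stands as far as it goes: a single fill-in analysed as observed is an inference from the wording. It does not remove the point, because the article states a method and a program. On the charitable reading SAS has no role and the sentence misdescribes the analysis; on the literal reading the inference is invalid.

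A reader might go further and infer that confidence intervals will be too narrow, or that the trial's type I error will be well above 5%. The article supports neither.
- It plans no confidence intervals. Coverage is used above only to express the error in the standard error.
- A simple two-group parallel comparison, with the post-test filled from the pre-test, gives a type I error of about 9% to 11% at 20% missing. That is not this trial, which is a four-condition crossover analysed by a mixed model. The 20% in the article is children leaving, not values missing.
- The article names only a kindergarten random effect. Null simulations of the crossover with single filling-in, a kindergarten effect and no child effect, and 20% of children leaving, gave type I errors of 4.1%, 1.4% and 0% at within-child correlations of 0.3, 0.5 and 0.7. With an assumed class-by-period variance of 0.03 they became 9.1%, 3.1% and 1.4%. The net error can fall on either side of 5%.

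The amount of missing data is also uncertain. The article presents heavy loss as a possibility and gives no figure beyond 20% dropout.

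**Conclusion.** The point holds in conditional form. The article separates missing-data handling from the model fit, and its wording most naturally means filling in scores before the analysis. If one completed data set is analysed as observed, the reported standard error is about 0.88 of the correct one at about 10% of values missing and about 0.75 at 20%, with p values correspondingly too small. The comparison is with the same model fitted to the observed scores, which kept coverage at 0.945 to 0.953.

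These sizes rest on a child random intercept, correlations of 0.3 to 0.7, the assumed dropout timing and missingness unrelated to the scores. They do not establish the trial's overall type I error, which also depends on the random-effects structure and is a separate issue. The sentence should be corrected on either reading.

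**What to change.** Replace the SAS sentence with a statement that the mixed model is fitted by (restricted) maximum likelihood directly to all observed scores, that this is valid under missing at random, and that no values are filled in beforehand. If imputation is used, for example as a sensitivity analysis, state that it is multiple imputation that respects the clustering and the repeated measures, with results pooled by Rubin's rules.

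The cost is one sentence, or two if a sensitivity analysis is named. Standard errors and p values will be somewhat larger than the filled-in analysis would report, which is the correction intended. No change to design, sample size or data collection is needed.

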**Methods:**

This program integrates fundamental movement skills training with cognitively challenging activities. Four classes per kindergarten will be randomly assigned to one of four conditions: (1) combined fundamental movement skills and cognitive challenge, (2) sedentary with cognitive challenge, (3) fundamental movement skills alone, or (4) sedentary without cognitive challenges. Each condition involves 30-minute sessions, three times per week, with a six-week washout period between the three-week intervention phases. The research team will use multiple objective measures and self-report measures, covering the elements and domains of the assessment of physical literacy and executive function. Three follow-up tests will be conducted within six months after the end of the intervention to evaluate the long-term impact of the program. Intervention implementation and fidelity will be assessed through focus group interviews with teachers and principals.

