### Intervention strategy

The AMPLE program comprises four intervention arms:aCombination Group (FMS with cognitive challenge)A series of FMS games with cognitive challenges will be implemented by trained teachers during classroom time. Each game will last 30 min and will be played 3 times a week for a total of 3 weeks. An example of a game with cognitive challenges running as FMS training: “connect 4 real version”, a board with 7 columns and 6 rows, 1.2 m long and 1 m wide, will be placed, with all participants standing behind a taped line 15 m away and a timer set for 30 min. The goal of the participants is to place their 4 game pieces on the large board as quickly as possible and keep the pieces in a straight line (horizontal, vertical, or diagonal lines are all allowed). The game is played in pairs, and once a participant has placed their piece and run back behind the tape line, the next participant is allowed to begin [19]. Throughout the game, all participants will be monitored for heart rate to ensure that their heart rate is maintained within 65% to 85% of their maximum heart rate.bCognitive Group (Sedentary with cognitive challenge).A series of games with only cognitive challenges will be implemented by teachers during classroom time. Each game will last 30 min and will be played 3 times a week. An example of the game is “connect 4 routine version”, all participants will be seated at a table to ensure a sedentary state, and a timer will be set for 30 min. The goal of the game is to place 4 of their own game pieces on the board and try to connect the pieces in a straight line. The game is played in pairs, and once one participant has placed his or her piece, the other participant will be allowed to place the piece.cPhysical Group (FMS without cognitive challenge).A series of games with FMS interventions will be implemented by the teachers during classroom time. Each game will last 30 min and will be played 3 times a week. An example of the game is as follows: a clearly marked chart with rounds will be placed, all participants will stand behind a taped line 15 m away, and a timer will be set for 30 min. Once a participant has run out, they need to mark the number of rounds on the chart as soon as possible and return; once they have returned, the next participant is allowed to start and repeat. Throughout the game, all participants will be monitored for heart rate to ensure that their heart rate remains within 65% to 85% of their maximum heart rate.dControl Group (Sedentary without cognitive challenge).All participants will not engage in any cognitive challenge or FMS interventions but will sit in their own seats while the teacher plays a 30-minute story appropriate for young children. All participants will be informed prior to the start of the program that they will not be asked any questions related to the video or story and ensure a state of minimal cognitive engagement.

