
### Washout period

In a cluster randomized crossover (CRXO) design, washout periods need to be carefully set to minimize the impact of the effects produced by the previous intervention on the next intervention [43]. The carry-over effects of psychological or behavioral interventions are difficult to measure accurately, and the optimal duration for a washout period has not yet been clearly established. In a study published by a team of Stanford University researchers on the effects of digital physical activity intervention on daily steps, the crossover process of four interventions did not have a washout period [44]. Some previous crossover designs related to PA interventions agreed that it is appropriate to set a washout period equal to the duration of the intervention period [45–47]. In addition, there is a need to consider the impact of young children’s own rapid development of motor skills and cognition in non-intervention situations. Therefore, this study hypothesizes that the carry-over effects of the intervention on young children will be greater than the rest of the lifespan, that the duration of the washout period will be set to be twice the length of the intervention period (3 weeks for the intervention period and 6 weeks for the washout period), and that pre-tests and post-tests will be implemented at each stage of the intervention to ensure the accuracy of the measurements

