### Data collection procedures

Data collection will follow a cyclical pattern: 1-week pre-test, 3-week intervention, 1-week post-test, and 6-week washout. This cycle will be repeated three times, followed by a final post-test at week 38 and three follow-up tests at 8-week intervals (weeks 46, 54, and 62). See Table 1 for the detailed schedule. In the CRXO design of this study, from the cohort perspective, each cluster is required to receive all 4 interventions sequentially; from the cross-sectional perspective, each cluster is required to receive 4 different interventions each at the same time; thus, a total of 24 combinations of the intervention sequence are generated (4*3*2). Since the effect of the intervention sequence on the results of the study will not be considered, this study will use GraphPad Software to randomly select the combination of the intervention sequence to be used in the study.

**Table 1 Tab1:** Schedule of the cluster randomized crossover trial

Schedule of Interventions 2025–2026		
20/10/2025-26/10/2025	1 week	Pre-test 1
27/10–16/11	3 weeks	Intervention 1
17/11–23/11	1 week	Post-test 1
24/11/2025-4/1/2026	6 weeks (Including Public Holiday for Christmas)	Washout period 1
5/1–11/1	1 week	Pre-test 2
12/1–1/2	3 weeks	Intervention 2
2/2–8/2	1 week	Post-test 2
9/2–22/3	6 weeks (Including Public Holiday for Spring Festival)	Washout period 2
23/3–29/3	1 week	Pre-test 3
30/3–19/4	3 weeks	Intervention 3
20/4–26/4	1 week	Post-test 3
27/4–7/6	6 weeks	Washout period 3
8/6–14/6	1 week	Pre-test 4
15/6 − 5/7	3 weeks	Intervention 4
6/7–12/7	1 week	Post-test 4
13/7 − 6/9	8 weeks (13/7–31/8 for washout, 1/9 − 6/9 for test)	Follow-up 1
7/9 − 1/11	8 weeks (7/9–25/10 for washout, 26/10 − 1/11 for test)	Follow-up 2
2/11–24/12	8 weeks (2/11–17/12 for washout, 18/12–24/12 for test)	Follow-up 3

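### The executive-function model compares conditions through an interaction with number of intervention days and does not tie the comparison to the post-test by assigned condition

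*Protocol article*

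**What the plan says.** In the protocol article, Data analysis names a linear mixed effects model for the association of the interventions with EF. Its time variable is a count of days, and the sentence that introduces it begins: "The number of intervention days (time) was considered to have a possible association with intervention effects [72], so the interaction between the two will be" … It ends by entering that interaction as a model term. The remaining structure is: "Fixed effects will include the intervention days and group, whereas the cluster (i.e., kindergarten) will be treated as a random effect". The comparison of conditions is stated separately: "Tukey’s honestly significant difference (HSD) test will be used to determine whether there is a significant difference between the interventions". False-discovery-rate correction is also mentioned. The same section computes Cohen's d from post-intervention group means, with no reference to days.

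The dose is planned to be equal. The abstract says "Each condition involves 30-minute sessions, three times per week, with a six-week washout period between the three-week intervention phases", and Intervention strategy says of the combination group "Each game will last 30 min and will be played 3 times a week for a total of 3 weeks".

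Outcomes are measured on both sides of each period. The cycle is "1-week pre-test, 3-week intervention, 1-week post-test, and 6-week washout", and Washout period confirms that "pre-tests and post-tests will be implemented at each stage of the intervention". Data collection procedures adds that "each cluster is required to receive all 4 interventions sequentially".

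**The concern.** The hypothesis on EF (H2) is about gains under each condition after the intervention. The natural estimate is the difference between assigned conditions at the scheduled post-test, or in change from that period's pre-test. The stated model puts a days variable and its interaction with condition in the way of that estimate. Once an interaction is present, a difference between the interventions has no single value. It depends on how days is counted and on the number of days at which the groups are compared.

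The article allows more than one count, and under two of the three plausible ones a plain comparison of groups can answer a different question from H2. At stake is an EF effect that is diluted or missed in the between-condition test, or one distorted because children who attend more differ from those who attend less. The p value and the Cohen's d could also describe different quantities, since d is taken from post-intervention means.

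**Working it through.** **Inputs from the protocol article.** Sessions per condition and period: 3 a week × 3 weeks = 9 (abstract; Intervention strategy). One pre-test and one post-test per period (Washout period; Table 1). Four periods per cluster. Classes and children: 18 × 4 = 72 classes of 11, 792 in all (Sample size calculations).

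**Assumed, not in the article.** Effect sizes, variances, attendance rates, and growth of the effect with sessions.

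**Formula.** For two conditions, E(Y) = a + b·G + c·D + e·G·D, with G the condition and D the days. The difference between conditions at D days is b + e·D. It equals b at zero days, b + e·(mean D) at average days, and b + 9e at the full course.

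**Reading 1: D = 0 at pre-test, 9 at post-test.** Suppose no baseline difference and an effect of 0.50 SD at post-test. Then b = 0 and 9e = 0.50, and mean D = (0 + 9)/2 = 4.5.
- At 0 days: 0.
- At mean days: 0.50 × 4.5/9 = 0.25.
- At 9 days: 0.50.

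A simulation (72 classes × 11 children × 4 periods, 40 runs, ordinary least squares) gave 0.01, 0.25 and 0.50. The whole effect is in the interaction.

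**Reading 2: D = sessions received in the period.** Because 9 are planned everywhere, D at post-test departs from 9 only through sessions not delivered or not attended.

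*Equal attendance, unrelated to ability* (90% assumed, effect proportional to dose, 0.50 SD at 9 sessions). Mean D = 9 × 0.9 = 8.1, and the expected as-assigned effect is 0.50 × 0.9 = 0.45.
- At 0 days: −0.09 (SE 0.41).
- At mean days: 0.45 (SE 0.045).
- Model without days: 0.45 (SE 0.045).

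The mean-days contrast is sound here; only the zero-day contrast is uninformative. The SE ratio, zero days to mean days, is √(1 + μ²/σ²), with μ = 9p and σ² = 9p(1 − p):
- p = 0.80: √(1 + 7.2²/1.2²) = 6.1
- p = 0.90: √(1 + 8.1²/0.9²) = 9.1
- p = 0.95: √(1 + 8.55²/0.654²) = 13.1

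*Attendance differing by condition and related to ability* (90% against 80%; log-odds of attending +0.5 per SD of the child effect; effect growing to 0.30 SD at 9 sessions).
- As assigned: 0.23 SD.
- Days-by-group model at mean days: 0.50 SD.
- Days-by-group model at zero days: 0.47 SD.

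The excess at mean days is 0.50 − 0.23 = 0.27 SD, so centring does not remove it. Both features are needed: attendance must differ by condition and must also relate to ability.

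**Reading 3: D cumulative over periods** (9, 18, 27, 36; effect constant at 0.50 SD).
- At 0 days: 0.52 (SE 0.11).
- At mean days: 0.50 (SE 0.045).

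D is then a linear period term and this bias does not arise. Only precision suffers if the comparison is read at zero days.

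**The case against.** The strongest reply is that the article fixes neither the count nor the test that would make the model fail. A reader might infer that days differs between post-tests only through missed sessions, that Tukey is applied to an uncentred zero-day coefficient, and that the comparison by assigned condition is therefore lost and H1–H5 go untested. The document does not support that chain:

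- The variable is glossed as time, so a pre/post or cumulative count is equally open. The section on evaluation of implementation mentions session logs but does not link them to the model.
- Tukey contrasts may be taken at average days. With equal, unrelated attendance this matches the as-assigned result (0.45 in both).
- Under the pre/post count, the group-by-time interaction is a conventional test of greater gain, and the article says the interaction is included.
- Group remains in the model, Cohen's d uses unadjusted post-intervention means, and the model is stated for EF rather than for all five hypotheses.

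These points stand. It is also fair that coding and centring are details an article may leave to a fuller document.

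What remains is not a missing detail. The article does choose number of intervention days as the time variable and does place the between-condition decision on a Tukey comparison of interventions, not on the interaction or a post-test contrast. Averaging over visits halves the effect under the pre/post count, and centring does not cure dependence of attendance on condition and ability. The latter is not far-fetched: the Background itself names fatigue and loss of positive emotions as possible reasons for null or adverse findings, though it does not say they reduce attendance.

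**Conclusion.** The concern holds in a limited form. The EF comparison is built on a days-by-condition interaction although planned dose is constant, and the article does not anchor it to the post-test by assigned condition.

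The consequence depends on the count of days. With a pre/post count, a Tukey comparison of groups yields the baseline difference or half the effect. With sessions received, it can be biased (0.50 against 0.23 SD in one assumed scenario), but at mean days it is unbiased when attendance is equal and unrelated to ability. With a cumulative count, this bias is absent.

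The halving follows from algebra, given a balanced baseline and equal weight to both visits. The other sizes are illustrative: they rest on assumed attendance and effect build-up, and the fits were ordinary least squares, not the planned mixed model. The documents do not show that the trial will miss an effect, nor that H1, H3, H4 or H5 are affected. The point should be settled before analysis.

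**What to change.** In the main EF model, replace number of intervention days by scheduled visit (pre-test, post-test) and period, both as categories, with a condition-by-visit term. Define each Tukey-adjusted contrast as the difference between assigned conditions at the scheduled post-test, or in change from that period's pre-test. Include all children tested, regardless of sessions attended. State that the same contrast underlies the p value and the reported effect size.

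Move sessions received to a separate exploratory dose-response analysis, labelled as observational and supporting no confirmatory claim.

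The cost is a few sentences in the analysis section and one extra exploratory model. No new data are needed.
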